### Collection of usual care data

A minimum of two scoping focus groups will be held prior to recruitment. Each will utilise a case analysis approach with clinicians providing treatment for sensory processing difficulties (one in each region). A small number of one-to-one telephone interviews may supplement focus group data as required. Focus groups will explore what is currently delivered/received as UC in the Health Boards/Trusts involved, and what if any difference exists in local provision and between regions (i.e. currently South Wales and England).

To develop a schedule for the focus groups, a brief survey will have been distributed to occupational therapist practice leads (OTs) in trial regions working with the trial population, via OT service leads.

Interviews with carers of children with ASD and sensory processing difficulties (parents from both South Wales and Cornwall) will be conducted. These will utilise a time-line facilitated process [31]. We will ask participants to focus on key points along a timeline, including ‘the beginning’, ‘diagnosis’, and ‘now’.

### Family carer and therapist interviews

Following the 6-month/post-intervention time point, interviews will be conducted with all SIT therapists (5–10 interviews) and a sample of family carers in both arms (anticipated to be 10–15 in each arm before data saturation).

Primary carers may choose to be interviewed alone or with other members of their family who are involved in day-to-day care. Participants will be asked to reflect on their experience of the intervention and the usual care activities that occurred alongside it, or their experience of usual care alone.

Therapists will be sampled to achieve variation in Health Board/Trust and regional centre and will be given the choice of telephone or face-to-face interviews. Family carers will be sampled to ensure maximum variation in terms of range of ASD and sensory symptoms, Health Board/Trust, and regional centre. Interviews will take place at a location of the interviewee’s choice, often their home, or over the phone.

The interview topic guides will be developed from a review of previous research, guides used by the research team in similar studies, and with input from the multi-disciplinary research team and family carer advisors to avoid bias in topic selection and wording of questions. The topic guide will be piloted and refined as necessary. Interviews will be recorded and transcribed.

### Safety reporting

No adverse events are expected. However, adverse events will be collected, recorded, and reported in accordance with Good Clinical Practice and the requirements of the research ethics committee. The Chief Investigator may carry out urgent safety measures if appropriate to protect participants from immediate harm.

### Sample size determination

We will recruit 216 participants in total (108 allocated to usual care, 108 allocated to the SIT intervention). This will provide 90% power at the 5% significance level (two-sided) to detect a standardised effect size of 0.5, allowing for 20% loss to follow-up at the primary outcome time point (6 months post-randomisation).

Our effect size is based on means and SDs of the ABC-I in relevant populations found in the literature [19, 32, 33]. This literature also suggests that a 25% relative difference represents a clinically meaningful difference on the ABC-I. Findings from the internal pilot will aid in confirming the accuracy of the assumptions behind the sample size calculation and could potentially lead to this being adjusted.

### Main analysis

The primary analysis will be based on the modified intention-to-treat (MITT) analysis population, and will estimate the between-group mean difference in the ABC-I at 6 months using linear regression, adjusting for baseline ABC-I, recruitment site, severity of SP difficulty, and sex of the child. If appropriate, therapist clustering will be accounted for using mixed models. Secondary outcomes will be analysed similarly.

### Sub-group analysis

Sub-group analyses will be conducted, exploring any differential intervention effects by site, region, age, sex of the child, severity of SP difficulties, adaptive behaviour, socialisation, motor skills, and comorbid conditions. This will be carried out by repeating the primary analysis but including each sub-group as an explanatory variable along with a sub-group × treatment arm interaction. Sub-group analyses will also be performed on carer stress.

### Impact of missing data and non-adherence

The impact that non-adherence to the intervention has on the intention-to-treat (ITT) findings will be investigated by estimating the complier-average causal effect (CACE) for the primary and secondary outcomes [34].

While the main trial analysis will be based on an MITT analysis population, sensitivity analyses will be carried out exploring the impact that missing data may have had on trial findings. Where outcome data are missing due to drop-out/loss to follow-up, these will be assumed to be missing at random given observed data (MAR), and multiple imputation will be used to achieve a full ITT analysis population. Additional sensitivity analyses will be conducted using joint modelling approaches (e.g. selection and/or pattern mixture models) to explore departures from an MAR assumption [35].

### Mediation analysis

Exploratory mediation analyses will be conducted to examine whether any effect of the intervention on behavioural problems at 1 year (all ABC subscales) is mediated through an effect on sensory sensitivities immediately post-intervention. The analyses will control for baseline measures of behavioural problems and SP difficulties to minimise any residual confounding between mediator and outcome [36]. Additional analyses will be conducted to explore the association between measures collected as part of the process evaluation and primary/key secondary outcomes. As the majority of process evaluation measures will only be collected for participants allocated to the SIT arm, the analysis will be purely associational and therefore hypothesis generating in nature.

### Exploratory analysis

Given the variability in the usual care that we are likely to see, we will conduct analyses using participants in the UC arm only that explore the association between different types of usual care and clinical outcomes. Parameters we will use to characterise different types of usual care will include number of treatment contacts, therapist experience/level of training, and type of difficulty for which the therapy is intended. Regression models will be fitted using our primary and secondary outcomes, and the therapy characteristics/parameters as explanatory variables. Variables that confound the relationship between therapy characteristics and outcome (e.g. age, severity of SP difficulty) will be investigated and controlled for in the models. The interpretation of the findings from these analyses will reflect the exploratory nature of this work and will be purely associational (that is, without ascribing cause).

A statistical analysis plan will provide further detail on analytical methods we will be using for the analysis of trial outcomes, and will be finalised prior to the end of recruitment.

### Qualitative analysis

Qualitative data will be analysed by the qualitative team using thematic analysis [37]. We will search across the data set to find repeated patterns of meaning, and identify key themes and sub-themes. We will identify contradictory data as points of contrast as well as similarities to understand uptake and engagement with the intervention. Vital measures will be put into place to ensure validity and reliability. Double coding will be carried out until consensus is reached. Data will be managed using qualitative coding software (such as NVivo10). This qualitative component has been designed using the principles of the Critical Appraisal Skills Programme qualitative checklist to ensure the quality of qualitative research [38].

### Health economic analysis

A within-trial health economic analysis will be conducted from a health and personal social services (NHS and PSS) perspective. The health economic analysis will be carried out on an ITT basis. The main analyses will compare cost and cost effectiveness at 6-month follow-up of SIT compared with UC. Total and mean costs for the SIT and UC group will be reported in a disaggregated format. Total and mean severity outcomes (ABC-I) will be reported for the intervention and control groups. The difference in mean scores between the two groups will be assessed with appropriate statistical tests. The difference in mean costs for the treatment groups will be analysed using regression analysis and bootstrapping. NHS and PSS costs (or societal costs in the secondary analyses) over the 6 months will be regressed on treatment allocation, baseline ABC-I, site, severity of SP difficulty, and baseline costs. We will account for clustering in the analysis.

An incremental cost-effectiveness ratio (ICER) will be calculated, defined as the difference in mean costs divided by difference in mean ABC-I as: the incremental cost per participant achieving a significant improvement in mean ABC-I score from an NHS/PSS perspective. Results will be plotted on a cost-effectiveness plane. Bootstrapping will be used to estimate a distribution around costs and behavioural outcomes and to estimate the confidence intervals around the ICER. Cost-effectiveness acceptability curves (CEAC), a recommended decision-making approach to dealing with uncertainty, will be generated by plotting these probabilities for a range of values of the ceiling ratio. Sensitivity analysis will be used to explore the sensitivity of the results from using a broader societal perspective (including NHS/PSS costs, education service costs, carer expenses, and lost productivity) than a narrower NHS/PSS perspective preferred by the NICE reference case [39]. Additional sensitivity analyses will build on results of the sub-group analyses.

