### Randomisation and blinding

Participants are assigned an identification number at consent. These are allocated sequentially for each site. Following screening, consent, and collection of baseline data, participants will be randomly allocated to usual care or SIT in a 1:1 ratio. Online randomisation will be carried out by the research team and will utilise minimisation with a random component used to allocate participants to the group that causes the least imbalance. Allocations will be minimised by site, severity of sensory processing difficulty, and sex of the child.

It will not be possible to blind recruiters to previous allocations. All data cleaning and manipulation prior to statistical analysis will be carried out blind to allocated treatment.

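### The cost regression omits sex, one of the three minimisation factors, and the economic section does not tie the ICER's ABC-I difference or its ITT label to the primary analysis.

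*Protocol article*

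**What the plan says.** All references are to the protocol article.

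- **Randomisation and blinding:** "Allocations will be minimised by site, severity of sensory processing difficulty, and sex of the child".
- **Main analysis:** the 6-month ABC-I difference is estimated by linear regression, "adjusting for baseline ABC-I, recruitment site, severity of SP difficulty, and sex of the child". On population: "The primary analysis will be based on the modified intention-to-treat (MITT) analysis population".
- **Impact of missing data and non-adherence:** as a sensitivity analysis under a missing-at-random assumption, "multiple imputation will be used to achieve a full ITT analysis population".
- **Health economic analysis, population:** "The health economic analysis will be carried out on an ITT basis".
- **Health economic analysis, costs:** costs "over the 6 months will be regressed on treatment allocation, baseline ABC-I, site, severity of SP difficulty, and baseline costs". The same model serves the NHS/PSS costs and, in secondary analyses, the societal costs.
- **Health economic analysis, effect:** "The difference in mean scores between the two groups will be assessed with appropriate statistical tests". The ICER is "defined as the difference in mean costs divided by difference in mean ABC-I as" the extra cost per participant with a significant improvement. Bootstrapping is planned for costs and behavioural outcomes and for the ICER interval.

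**The concern.** An analysis should normally adjust for the factors used to balance the allocation. Minimising on a factor removes most of its chance imbalance. A model that omits the factor still counts its contribution to the outcome as noise, so it overstates the uncertainty of the treatment difference. The primary model follows this rule for all three factors. The cost model follows it for two of the three, and because its covariates are listed one by one, the omission is stated text and not a detail left for later.

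The second issue is traceability. The ICER divides a cost difference by an ABC-I difference at 6 months, and the primary analysis already estimates that ABC-I difference. The economic section does not refer back to it, names no model for the effect, and uses a different population label. Two analysts could therefore follow the text faithfully and put different ABC-I differences into the ICER, and one of these might not match the trial's headline result. Cost effectiveness is a stated secondary objective and half of the question posed in the Discussion, so the link should be explicit.

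**Working it through.** **Step 1. The covariate sets side by side.**

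| Factor | Minimisation | Primary ABC-I model | Cost model |
|---|---|---|---|
| Site | yes | yes | yes |
| Severity of SP difficulty | yes | yes | yes |
| Sex | yes | yes | **no** |
| Baseline ABC-I | no | yes | yes |
| Baseline costs | no | no | yes |

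Baseline costs belong only in the cost model, so that difference is expected. Sex is the only minimisation factor missing, and no reason is given.

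**Step 2. Size of the omission.** The article gives no cost variance and no relation between sex and cost, so the share of variance is an assumption. Let R² be the share of cost variance, after the other covariates, that sex explains. If minimisation balances sex between the arms, the true variance of the cost difference is proportional to (1 − R²). The model without sex estimates it as if R² were zero. Hence

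model SE / true SE = 1/√(1 − R²),

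and a nominal two-sided 5% test has true size 2 × [1 − Φ(1.96/√(1 − R²))].

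| Assumed R² | SE ratio | SE too large by | True size of a 5% test |
|---|---|---|---|
| 1% | 1/√0.99 = 1.005 | 0.5% | 4.9% |
| 2% | 1/√0.98 = 1.010 | 1.0% | 4.8% |
| 5% | 1/√0.95 = 1.026 | 2.6% | 4.4% |
| 10% | 1/√0.90 = 1.054 | 5.4% | 3.9% |

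The error is conservative. Because sex is balanced by design, omitting it causes no expected bias in the cost difference. The minimisation has a random component, so balance is approximate and so are these ratios.

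**Step 3. The effect side of the ICER.** Three statements bear on it. The Main analysis section gives an adjusted regression on MITT. The economic section says the difference in scores will be tested, without naming a model or covariates. The ICER definition says only that the denominator is a difference in mean ABC-I. None of them says whether the denominator is the adjusted primary estimate, a raw difference, or a separate model.

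**Step 4. Population.** The primary analysis is on MITT and the economic analysis on ITT. The missing-data section reaches a full ITT set by multiple imputation. The economic section does not say that it uses this set.

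**Step 5. Stated figures.** The plan gives no figure for this point. Its sample size reproduces and is unaffected: for 90% power, two-sided 5% and a standardised effect of 0.5, the t-based calculation gives 86 per arm; 86/0.8 = 107.5, rounded up to 108 per arm, or 216 in total.

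**The case against.** The strongest reply is that this is minor. By the figures above, leaving out sex costs about 1% to 3% in the standard error under plausible assumed shares, introduces no expected bias, and errs on the safe side. The model already carries site, severity, baseline ABC-I and baseline costs. That stands, and it limits the weight of the point. It does not justify the omission, since sex is already collected and used in the primary model.

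It can also be said that ITT for the economic analysis is a legitimate stated choice, that an imputed ITT set is already planned, and that the article uses the labels loosely, since its non-adherence paragraph calls the trial's results ITT findings. A health economics or statistical analysis plan, not shown here, may supply the link. This also largely stands. What remains is that the passages should be tied together.

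A reader might go further and infer that the ICER sets an adjusted cost difference over an unadjusted ABC-I difference, because costs get a named regression while scores get only unnamed tests. The text does not support this. It neither calls the ABC-I difference unadjusted nor excludes the primary model, and it does not say that those tests supply the denominator. Any loss of precision worked out from an assumed baseline-to-6-month correlation would therefore quantify an analysis that the article does not state.

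A reader might also infer that mismatched covariates destroy the correlation between cost and effect needed for the cost-effectiveness plane and acceptability curve. They do not. Resampling each child with both cost and outcome keeps that correlation whether or not either difference is adjusted, and nothing in the section says that costs and outcomes are resampled separately.

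**Conclusion.** The point holds as a consistency defect of small size. It is established that the cost regression omits sex, which is a minimisation factor and a primary-model covariate, without a reason. It is also established that the economic section does not link its ABC-I difference to the primary estimate and uses ITT where the primary analysis uses MITT.

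For the omission of sex, the range of about 1% to 3% rests on an assumed 2% to 5% of residual cost variance and on near balance from minimisation. Even at 10% the standard error would be only 5.4% too large.

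No size can be given for the missing link, because the documents do not say which ABC-I difference would be used. They do not show that the denominator is unadjusted, that two conflicting effects will be reported, or that the cost-effect correlation is lost.

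**What to change.** In the Health economic analysis section, or in the analysis plan that governs it:

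1. Add sex to the covariates of the cost regression, for both the NHS/PSS and the societal cost models.
2. State that the ABC-I difference in the ICER is estimated with the primary model's covariates (baseline ABC-I, site, severity of SP difficulty, sex), and that this model and the cost model are refitted in the same bootstrap resamples.
3. State that the economic ITT data set is the multiply imputed set described under missing data, or otherwise reconcile it with the MITT population of the primary analysis. If the imputed set is used, say that missing costs are imputed too and how imputation and bootstrap are combined.

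The cost is a few sentences and some code. No new data are needed, and the sample size and trial conduct do not change.

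### The bootstrap confidence interval planned around the ICER cannot be interpreted if the ABC-I difference is not clearly away from zero, and the article attaches no condition to it (minor)

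*Protocol article*

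**What the plan says.** In the protocol article, the Health economic analysis section sets the main comparison at 6 months: "The main analyses will compare cost and cost effectiveness at 6-month follow-up of SIT compared with UC". The ICER is "defined as the difference in mean costs divided by difference in mean ABC-I". Its uncertainty is to be handled as follows: "Bootstrapping will be used to estimate a distribution around costs and behavioural outcomes and to estimate the confidence intervals around the ICER". No condition is attached, the type of bootstrap interval is not named, and nothing is said about replicates that fall in more than one quadrant.

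The same section plans two displays of joint uncertainty. For the plane: "Results will be plotted on a cost-effectiveness plane". The acceptability curves "will be generated by plotting these probabilities for a range of values of the ceiling ratio".

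The precision to expect follows from the Sample size determination section, which sets 216 children at 108 per arm: "This will provide 90% power at the 5% significance level (two-sided) to detect a standardised effect size of 0.5". That number already includes an attrition allowance of 20% at 6 months.

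**The concern.** An ICER is a ratio, and its sign alone does not say which quadrant it came from. A negative ratio can mean cheaper and better, or costlier and worse. A positive ratio can mean costlier and better, or cheaper and worse. While all replicates have an effect difference of one sign, ranking the ratios is harmless. Once an appreciable share cross zero effect, the ranking breaks down. A costlier-and-worse replicate gets a negative ratio and is placed below every costlier-and-better replicate, although it is the least favourable result. Ratios close to the crossing run off to plus or minus infinity.

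Cost-effectiveness is one of the trial's stated aims, and a small or null effect on ABC-I is a realistic result: the Background calls the evidence for SIT limited, and the Discussion allows that SIT may not be effective. In that case the promised interval could be read as allowing a cost saving when hardly any replicate shows one.

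**Working it through.** **Precision, starting from the plan's own figure.** For an effect of 0.5 SD, 90% power and two-sided 5%, about 85 per arm are needed. 85/0.8 = 106.25, so 107 per arm or 214 in total, in line with the stated 216. With 20% loss, 108 × 0.8 = 86.4 per arm are analysed (power about 90%).

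SE of the standardised difference = √(2/86.4) = 0.152 SD. If baseline ABC-I correlates 0.6 with the 6-month score (assumed), the factor √(1 − 0.36) = 0.8 gives 0.122 SD.

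**When replicates straddle zero.** Under a normal approximation, the share of replicates on the wrong side is Φ(−d/SE), with d the observed effect (positive = benefit). It exceeds 2.5% when d < 1.96 × SE, that is 0.298 SD, or 0.239 SD with the assumed correlation.

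| Observed d (SD) | Wrong side, SE 0.152 | Wrong side, SE 0.122 |
|---|---|---|
| 0.1 | 25.6% | 20.6% |
| 0.2 | 9.4% | 5.0% |
| 0.3 | 2.4% | 0.7% |
| 0.5 | 0.05% | 0.002% |

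**How likely that is.** With SE 0.152, the chance of an observed difference inside ±0.298 SD is 9% if the true effect is 0.5 SD, 50% at 0.3, 74% at 0.2, 90% at 0.1 and 95% at 0.

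**What a percentile interval would report.** The article gives no cost figures, so these are assumptions: a cost difference of 600, 1500 or 3000 with SE 300 (2, 5 or 10 standard errors), uncorrelated with effect. The percentile limits come from normal draws with effect SE 0.152. The comparison is Fieller's 95% set, all R with (C − R·d)² ≤ 1.96²(SE_C² + R²·SE_E²). Worked in standard-error units for C = 1500, d = 0.2: C/SE_C = 5 and d/SE_E = 1.3145, so (5 − 1.3145R)² ≤ 3.84(1 + R²). This reduces to −2.11R² − 13.15R + 21.16 ≤ 0, so R ≤ −7.55 or R ≥ 1.33. Multiplying by 300/0.152 gives costs per SD.

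| Cost difference | Observed d | Percentile interval (per SD) | Fieller 95% set (per SD) |
|---|---|---|---|
| 600 | 0.2 | about −23,000 to 30,000 | ≤ −5,000 or ≥ 60 |
| 1500 | 0.2 | about −59,000 to 72,000 | ≤ −14,900 or ≥ 2,600 |
| 3000 | 0.2 | about −119,000 to 145,000 | ≤ −30,400 or ≥ 5,800 |
| 1500 | 0.5 | about 1,500 to 7,700 | 1,500 to 7,800 |

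At 0.5 SD the two agree. At 0.2 SD the percentile interval contains the whole excluded range, including zero and modest negative ratios, and it cuts off both unbounded tails. At a cost difference of 1500 or 3000, virtually no cost replicate is a saving. With SE 0.122 and cost 1500, the contrast at 0.2 SD is the same in kind: about −39,000 to 61,000, against ≤ −38,400 or ≥ 2,900.

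**Coverage.** In 3,000 simulated trials of 1,000 replicates each (cost 2, 5 or 10 SE above zero, correlation 0 or −0.3), the nominal 95% percentile interval covered 96–98% for true effects of 0.1 to 0.5 SD, 91–94% at 0.05 SD and 0% at 0.001 SD. Fieller's set stayed at 94–96%.

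**The case against.** Four arguments can be made for the plan as it stands.

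- *The percentile construction is assumed.* This is correct. A bootstrap interval ordered by angle on the plane would also fit the text and would not mix quadrants in the way shown, so the percentile figures above are conditional. But when the effect is not clearly non-zero, the correct set of ratios is unbounded, and no finite interval of any type represents it.
- *Interval type is detail for the full protocol or analysis plan.* This is true of the interval type, and silence on it would be no finding. Here, however, the article positively commits to an ICER interval whatever the result.
- *The plane and CEAC already show the joint uncertainty.* They do, and both stay valid when the ICER interval does not. This limits the harm, but neither supplies the interval that is promised.
- *The definition is not single.* The same sentence also glosses the ICER as a cost per participant who improves. A denominator of that kind would change the SD thresholds above, but not the argument about a denominator near zero.

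A reader might infer something stronger: that the interval is statistically invalid whenever the primary ABC-I comparison is non-significant. The document and the calculations do not support that. Simulated coverage is close to nominal or slightly conservative except when the true effect is almost zero. Nor is the trigger tied exactly to the primary test, because the economic analysis is on an ITT basis and the primary analysis on a modified ITT population.

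**Conclusion.** The point holds as one of interpretation. The article commits without condition to an interval that has no usable meaning when bootstrap ABC-I differences lie on both sides of zero. That means an observed effect below roughly 0.30 SD, or 0.24 SD under an assumed baseline correlation of 0.6. Such a result has a 9% chance even at the planned effect of 0.5 SD and a 74% chance at a true 0.2 SD (unadjusted SE).

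The thresholds rest on 86.4 analysed per arm and a normal approximation. The monetary intervals rest on assumed costs, zero cost-effect correlation and percentile limits, and serve only as illustration. One secondary economic summary is affected; the primary clinical conclusion, the plane and the CEAC are not. It is a minor point.

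**What to change.** In the health economic analysis, replace the unconditional ICER interval with these steps:

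1. Report incremental net monetary benefit (ceiling ratio × effect difference − cost difference) with its bootstrap 95% CI, at the same ceiling ratios as the CEAC.
2. Give the ICER as a point estimate.
3. Quote an ICER interval only when at least 97.5% of the economic-analysis replicates lie on one side of zero effect, and name its type. Otherwise rely on the plane, the CEAC and net benefit.

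Net benefit is linear in both differences, so its interval stays finite. With d = 0.2 SD (SE 0.152), cost 1500 (SE 300) and an assumed ceiling of 10,000 per SD, it is 2,000 − 1,500 = 500, with SE √(1,521² + 300²) = 1,551 and 95% CI 500 ± 1.96 × 1,551, about −2,540 to 3,540.

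The cost is about a sentence of text and one extra reported summary from the same replicates. No new data or resampling are needed. Net benefit does have to be read against a stated ceiling ratio per unit of ABC-I, but the CEAC already requires a range of these.
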